# Simulation TRaining for Operative vaginal Birth Evaluation: study protocol for an observational stepped-wedge interrupted time-series study (STROBE)

**DOI:** 10.1186/s12884-019-2222-x

**Published:** 2019-04-02

**Keywords:** Training, Birth, Operative vaginal birth, Forceps, Ventouse, Outcomes

## Abstract

**Background:**

Operative vaginal birth is a common procedure used to expedite birth after full cervical dilatation where there is a clinical need to do so (15% of births in the UK in 2016). The acquisition of skills for operative vaginal birth is dependent on the exposure of junior obstetricians to situations in which they can undertake directly supervised learning from senior accouchers. The Royal College of Obstetricians and Gynaecologists has recently introduced the first structured course in operative vaginal birth. To date, there have been no attempts to determine the clinical impact of a structured training package for operative vaginal birth.

**Methods:**

The STROBE study is a quasi-experimental before-after interrupted time-series study of the effect of simulation training in operative vaginal birth for obstetricians on clinical outcomes of women and babies following operative vaginal birth. Similar to a stepped-wedge design, the intervention will be gradually implemented in all participating units but at different time periods. The primary outcome is failed operative vaginal birth with the first intended instrument. Secondary maternal outcomes are; use of second instrument to achieve operative vaginal birth, caesarean section, episiotomy, perineal trauma (1st, 2nd, 3rd, 4th degree tear), cervical tear requiring suturing, general anaesthesia and estimated blood loss. Secondary neonatal outcomes are; Apgar score at one, five, and ten minutes, Umbilical artery pH, shoulder dystocia, admission to Neonatal Intensive Care Unit and death within 28 days of birth. The analysis will be intention-to-treat (per unit) on the primary and secondary outcomes. The STROBE study received approval from the Health Research Authority and is sponsored by North Bristol NHS Trust. Results will be published in an open-access peer-reviewed medical journal within one year of completion of data gathering.

**Discussion:**

The STROBE study will help establish our understanding of the effectiveness of locally-delivered simulation training for operative vaginal birth. Robust evidence supporting the effectiveness of such an approach would add weight to the argument supporting regular, local training for junior obstetricians in operative vaginal birth.

**Trial registration:**

ISRCTN11760611 05/03/2018 (retrospectively registered).

**Electronic supplementary material:**

The online version of this article (10.1186/s12884-019-2222-x) contains supplementary material, which is available to authorized users.

## Background

Complications of the second stage of labour (fetal distress, obstructed labour, maternal exhaustion or medical condition requiring shortening of the second stage of labour) remain a major cause of maternal and neonatal mortality and morbidity across the world – such complications are responsible for 4 to 13% of maternal deaths in Africa, Asia, Latin America and the Caribbean [1], and in 2013 obstructed labour alone accounted for 0.4 deaths per 100,000 women worldwide [2].

These complications can be mitigated by the accoucheur performing either an operative vaginal birth (OVB) or a caesarean section - when performed in an appropriate setting by skilled accoucheurs, OVB can reduce adverse outcomes for women and their babies relative to caesarean section [3], and remains a useful and viable strategy for the management of complications in the second stage of labour [4].

OVB is a complex skill that requires an understanding of the anatomy, constant re-evaluation of the situation, fine motor skills that respond to haptic feedback, and continuous simultaneous communication with both professional colleagues and the patient – axiomatically, this takes time to learn [5]. At present, the majority of useful learning by junior accoucheurs is conducted via ‘learning-on-the-job’, performing either parts or whole OVBs under direct, often hands-on supervision from a senior accoucheur [6].

Various attempts have been made in different settings to standardise and improve maternal and neonatal outcomes in OVB, including the provision of dedicated senior labourists [7, 8] and training junior accouchers in the use of forceps prior to the use of ventouse [9]. While these have shown increases in the rate of OVB performed, no changes in maternal or neonatal outcomes have yet been demonstrated. Moreover, no studies have examined the impact of attempts to increase practitioner skills and thereby clinical outcomes in more than one setting – all previous studies have been limited to locally implemented strategies alone.

In response to this clear need to provide structured OVB skills training to junior accouchers, the Royal College of Obstetricians and Gynaecologists (RCOG) has developed a structured training course to ensure provision of OVB skills to junior accouchers during their training, the RCOG Operative Birth Simulation Training course, (ROBuST). In 2017 the ROBuST course was introduced as a compulsory part of the speciality training curriculum for junior obstetricians in the UK. However, the impact of this course has not been evaluated. Our study seeks to determine the impact of structured training in OVB for junior accouchers on routinely collected maternal and neonatal outcomes across 4 large maternity units (Structured Training in Operative vaginal BirthE – the STROBE study).

## Methods

### Study design

This is a quasi-experimental before-after interrupted time-series study investigating routinely collected maternal and neonatal outcomes after OVB covering a time period which includes delivery of local simulation courses in OVB. Details of the study design are presented in Table 1. Similar to a stepped-wedge design, the intervention, local simulation courses in OVB, will be gradually implemented in all participating units with outcome measures collected before and after the implementation of the intervention. No data is collected for the time-period during which the training will be implemented. Randomisation of the training implementation period is not possible due to the participating units requiring the training intervention at specific times.

**Table 1 Tab1:**
[figure not shown]
SPIRIT diagram for the STROBE Study

If a participating unit is unable to implement the intervention, it will be considered as a control site allowing us to account for any potential change, independent of our study, in the clinical context surrounding OVB and its management. The STROBE guidelines were adhered to in the design of this study.

### Intervention studied

The intervention studied will be the local provision of structured simulation training in operative vaginal birth (the ROBuST course) to trainees in O&G in the South West of England. The intervention will be delivered by local faculty of senior obstetricians and midwives. The ROBuST course is a one-day course that utilises simulation models to teach the spectrum of operative birth manoeuvres – rotational and non-rotational forceps and vacuum deliveries, as well as techniques for complex caesarean sections.

### Participants

The study population will consist of women and babies having an attempted OVB in the four maternity units during the study period (12 months per site, between 700 to 850 women per site, at least 3000 women in total).

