### Primary outcome measure

The primary outcome measure will be failed operative vaginal birth with first chosen instrument. This has been chosen as failure with the first instrument will lead to either use of a second instrument or reversion to caesareans section – both of which have been demonstrated to be independently associated with poorer outcomes than success with the first instrument [3, 10]. Moreover, this is the chosen primary outcome of the most recent Cochrane review of the subject [11].

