#### Baseline and intervention description

The total and unit-specific number of births (count), OVB (count), failed attempted OVB (count) and rate of failed attempted OVB (%) will be tabulated by step/period (zero to five).

The frequency and proportion of staff trained and number of training sessions delivered by in-house trainers will also be reported for each of the 4 units. Proportions, means with standard deviation or median with inter-quartile range will be reported as appropriate to describe the maternal and neonatal outcomes.

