#### Main analysis

The outcome for the main analysis is the rate of successful attempted OVB in term infants, dichotomised into successful or failed. This dichotomous outcome measured for each birth will be analysed with a modified Poisson regression (with robust estimation of the variance) [16]. All models will be adjusted for hospital units as fixed to account for clustering at maternity unit level, i.e. correlation between births occurring in the same maternity unit. A formal mixed or marginal regression model cannot be considered due to the reduced number of hospital units involved in this study (n = four).

In the main analysis, we will assess the intervention effect (control periods vs. post-intervention periods) and include an adjustment for the time period (period zero to five) to account for any underlying time trend susceptible to confound the assessment of the main effect [17, 18]. We will either model the time periods with categorical fixed effect variables (with dummy indicators for each period) or as a continuous factor with appropriate polynomial function of time if required. Statistics such as the Aikeke information criterion will be used to select the best modelling for time.

The interaction between time and the main intervention effect will then be modelled to investigate the timing and duration of the intervention effect. The study is not powered for such interaction and this last model should be considered as exploratory.

We will use the Log-likelihood ratio or Wald test and *p*-value of 0.05 to assess the strength of the association, assuming that any p-value equal or below 0.05 (two-sided) will show evidence of an association between the intervention and outcome.

No interim analysis is planned.

The model will then be adjusted for patient, delivery or hospital characteristics susceptible to influence the primary or secondary outcome such maternal BMI, length of second stage of labour and fetal weight. These analyses will be conducted on an intention-to-treat principle, i.e. a unit will be considered as exposed to the intervention 3 months after the initial planed date of intervention implementation.

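### Every modelled outcome is conditional on an attempted OVB, a group the training may change; model the attempt rate beside the primary result

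*Protocol article*

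**What the plan says.** The Participants section defines the population: "The study population will consist of women and babies having an attempted OVB in the four maternity units during the study period". The inclusion criteria require that forceps or vacuum was applied to the fetal head. The primary outcome follows from this: "The primary outcome measure will be failed operative vaginal birth with first chosen instrument". The Main analysis section keeps the same denominator: "The outcome for the main analysis is the rate of successful attempted OVB in term infants, dichotomised into successful or failed". The secondary outcomes, caesarean section included, are collected in this same group, and no attempt rate is listed among them.

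Three other places bear on the point.

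- Background, on earlier efforts (dedicated senior labourists, forceps training before ventouse): "While these have shown increases in the rate of OVB performed, no changes in maternal or neonatal outcomes have yet been demonstrated".
- Intervention studied, where the course covers forceps and vacuum "as well as techniques for complex caesarean sections".
- Baseline and intervention description, where a table by unit and step is to hold "The total and unit-specific number of births (count), OVB (count), failed attempted OVB (count"), with the failure rate. No model is attached to the births or OVB counts.

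On case mix, the Main analysis section says: "The model will then be adjusted for patient, delivery or hospital characteristics susceptible to influence the primary or secondary outcome". It gives BMI, length of second stage and fetal weight as examples.

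**The concern.** Whether to apply an instrument is decided after training, in units whose doctors have been trained. The denominator is thus formed after the intervention and may respond to it. If trained doctors decline harder cases, or take on more of them, failures per attempt will move even if skill with the instrument is unchanged. Period terms remove time trends shared by the units. They do not remove a change in selection that begins in each unit when training begins.

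The Discussion says a positive result would be robust evidence for providing such training, and that an equivocal or negative one should prompt its redesign. Selection could distort either conclusion, and no planned model would estimate it.

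**Working it through.** The protocol gives no figure for the attempt rate, so there is none to reproduce. Its design figures are a failure rate of 20% falling to 10% (Sample size section), a relative fall of (20 − 10)/20 = 50%.

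**1. What selection alone can do.** Start from 100 attempts with 20 failures, the protocol's 20%. The numbers moved and their failure risks are assumptions; no such figures are in the document. Total births and skill are held fixed.

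| Change after training | Attempts | Failures | Failures per attempt | Attempts per birth, ratio | Failures per birth, ratio | First-instrument successes |
|---|---|---|---|---|---|---|
| None | 100 | 20 | 20.0% | 1.00 | 1.00 | 80 |
| A. 10 hard cases (50% risk) go straight to caesarean | 90 | 20 − 5 = 15 | 15/90 = 16.7% | 0.90 | 15/20 = 0.75 | 75 |
| B. 10 easy cases (5% risk) added | 110 | 20 + 0.5 = 20.5 | 20.5/110 = 18.6% | 1.10 | 20.5/20 = 1.025 | 89.5 |
| C. 10 hard cases (50% risk) added | 110 | 20 + 5 = 25 | 25/110 = 22.7% | 1.10 | 25/20 = 1.25 | 85 |
| D. A and B together | 100 | 20 − 5 + 0.5 = 15.5 | 15.5% | 1.00 | 15.5/20 = 0.775 | 84.5 |

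The range for A:

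- 5% of attempts diverted: 18.4% if half would have failed, 15.8% if all would have.
- 10% of attempts diverted: 16.7% if half would have failed, 11.1% if all would have.

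To produce the whole design effect, solve (20 − x)/(100 − x) = 0.10. This gives x = 10/0.9 = 11.1, so about 11% of attempts would have to be diverted, every one a certain failure.

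**2. Which companion measure shows it.** In A, failures per birth fall 25%, more than the 17% fall per attempt, so that measure would show a larger spurious benefit. In C it rises 25%, against 14% per attempt (22.7/20), although five more women deliver with the first instrument. The attempt rate moves in A, B and C and flags each. In D it does not move, so a stable attempt rate is not proof of stable case mix.

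**3. How precisely the attempt rate can be estimated.** Assume Poisson counts with no extra variation, fixed unit and period effects, and 250 attempts per unit per period (the protocol's expected figure, read as per unit). The standard error of the log rate ratio is the square root of the intervention element of (X′WX)⁻¹, with W = 250 in each observed cell.

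- Full Table 2 layout (20 cells): SE 0.068. The 95% interval factor is exp(±1.96 × 0.068), or 0.87 to 1.14. Power for a 10% fall is Φ(0.105/0.068 − 1.96), about 34%.
- At most two periods before and two after training in each unit (14 cells, nearer the stated 12 months per site): SE 0.107, interval factor 0.81 to 1.23, power about 16%.

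A non-significant change in attempts would therefore be weak reassurance.

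**The case against.** The protocol asks about outcomes following OVB and justifies its primary outcome on that basis. It also plans a case-mix adjustment and collects indication, rotation, parity and operator grade, although the Clinical variable characteristics section ties these to secondary outcomes. The tabulated counts would let a reader see a large shift in attempts. The textual support is modest: the earlier initiatives raised the OVB rate, which is the opposite direction to diversion, and teaching caesarean technique is not the same as changing the decision to attempt. The illustrative effect is well short of the 50% fall the study seeks, and supplementary models are often left to an analysis plan.

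Much of this stands, and it limits the point. A reader might infer that the study cannot distinguish skill from selection at all. That goes too far, because the adjusted model accounts for measured difficulty among attempts. A reader might also infer that training will divert hard cases to caesarean. Nothing in the document shows this; it only gives reason to think the attempted group can change.

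Two things do not stand. Adjustment among attempts cannot reach unmeasured difficulty, nor women who never enter the group. A descriptive table gives no estimate of a training-related change in attempts net of unit and period.

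**Conclusion.** The point holds as a limit on interpretation, not as a fault in the primary outcome. The modelled outcomes are all conditional on a group formed after training, and no planned model estimates whether training changed that group. Diverting 10% of attempts, half of them would-be failures, lowers the failure rate from 20% to 16.7%. The whole 20% to 10% effect needs about 11% diverted, all would-be failures, so selection is more likely to colour a result than to create all of it. These sizes rest on assumed diversion fractions and failure risks.

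It may be tempting to conclude that failures per all births should be the corrective analysis. The arithmetic does not support that, since the measure exaggerates the apparent benefit under diversion and the apparent harm when more hard cases are attempted.

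**What to change.** Keep failure per attempt as the primary outcome and add one pre-specified companion model:

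- **Model.** Attempted OVB per eligible birth, as counts with a log(births) offset and the same unit, period and intervention terms as the main analysis.
- **Definitions.** Define births to match the eligibility rules (singleton, aged 18 or over, not a prisoner) and the term restriction that appears in the Main analysis section. Confirm that the tabulated OVB count means attempted OVB.
- **Reporting.** Give the estimate and confidence interval beside the primary result. State in advance what change in attempts would be material, and qualify any claim of improved skill if the interval does not exclude it. Do not rely on a non-significant test.
- **Supporting results.** First-instrument successes and failures per birth may be shown if read jointly with the attempt rate. Failures per birth must not be used alone.

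The cost is one model on counts largely planned already, plus the work of restricting the births count to eligible births. The conclusion becomes somewhat more cautious: with four units the interval will be wide, so some qualification is likely even if attempts did not change. A stable attempt rate would still leave offsetting case-mix changes possible. Counting second-stage caesareans without an attempt would show diversion more directly, but those births are not among the planned counts and would need extra data.

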### Inclusion criteria

Data will be included in data collection and analysis if all of the following apply:A vaginal birth was conducted within a study site during the applicable study time periodAn operative vaginal birth instrument (forceps or vacuum) was applied to a fetal head

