### Exclusion criteria

Data from births will not be included in collection and analysis if any of the following apply:An operative birth instrument was only applied during (and not before) a caesarean section (i.e. use of Wrigley’s forceps at caesarean)The woman had a multiple pregnancy (twins or higher)If the woman is < 18 years old at the time of birthIf the woman is a prisoner

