### Secondary outcome measures

The following secondary maternal outcomes measures will be collected; use of second instrument to achieve OVB, caesarean section, episiotomy, perineal trauma (1st, 2nd, 3rd, 4th degree tear), cervical tear requiring suturing, general anaesthesia and estimated blood loss (EBL). The following secondary neonatal outcomes will be collected; Apgar score at 1, 5, 10 min, Umbilical artery pH, shoulder dystocia, admission to Neonatal Intensive Care Unit (NICU), death within 28 days of birth.

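### As worded, the inclusion criteria require a vaginal birth, which removes first-instrument failures that end in caesarean from the primary outcome and its denominator

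*Protocol article*

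**What the plan says.** The Inclusion criteria section sets a joint rule: "Data will be included in data collection and analysis if all of the following apply". The first condition is "A vaginal birth was conducted within a study site"; the second is that forceps or vacuum was applied to the fetal head.

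Four other sections bear on the same births:

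- Participants defines the population as "women and babies having an attempted OVB in the four maternity units during the study period".
- Exclusion criteria removes caesareans only where "An operative birth instrument was only applied during (and not before) a caesarean section".
- Primary outcome measure states "The primary outcome measure will be failed operative vaginal birth with first chosen instrument", and justifies this on the ground that "failure with the first instrument will lead to either use of a second instrument or reversion to caesareans section".
- Secondary outcome measures lists "use of second instrument to achieve OVB, caesarean section, episiotomy", among others.

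The Baseline and Main analysis sections also speak of attempted procedures, classed as failed or successful. Nothing in the article says that the first inclusion criterion is to be read more widely than it is written.

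**The concern.** A woman whose first instrument fails and who is delivered by caesarean meets the second inclusion criterion but not the first. Because both must hold, she is outside the dataset. So is a woman in whom a second instrument also fails before caesarean. These births leave the numerator and the denominator of the primary outcome together, so entry to the study depends on the outcome being studied.

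Three things are at stake. The failure rate is understated. Caesarean section, as a secondary outcome, cannot occur. And the before-after comparison becomes sensitive to what operators do after a failure, not only to how often they fail. The last point is plausible here, because the section on the intervention says that the course covers difficult caesarean technique as well as forceps and vacuum. Training could therefore alter the choice between a second instrument and caesarean.

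The planned analysis cannot repair this. Adjustment for unit, period and case mix does not restore births that were never collected, and the missing-data sensitivity analyses concern births already in the dataset.

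**Working it through.** **Reading the sections together.** If the first criterion is taken literally, the caesarean exclusion is redundant, one of the two failure routes in the primary outcome is unobservable, and one listed secondary outcome is always zero. If births by either route are admitted, all the sections agree. The wording of the first criterion is therefore the odd one out.

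**Inputs.**

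- True first-instrument failure before training, *f* = 20%. This is the complement of the 80% success rate in the section on the frequency of the primary outcome.
- Failure after training under the planned effect: 10% (Sample size, conservative estimate).
- Share of first-instrument failures that end in caesarean, *c*. The protocol gives no figure. Assumed 25% to 50%, with 10% to 60% shown as a wider range.

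**Formula.** Of *N* attempts, *Nf* fail and *Nfc* end in caesarean and are dropped. What remains is *N*(1 − *fc*) births, with *Nf*(1 − *c*) failures:

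observed failure = *f*(1 − *c*) / (1 − *fc*)

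For *f* = 0.20 and *c* = 0.25: 0.15 / 0.95 = 15.8%. For *c* = 0.50: 0.10 / 0.90 = 11.1%. The births lost before training are *fc* = 5% and 10% of all attempts.

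**Case 1: *c* is the same before and after training, true change 20% to 10% (risk ratio 0.50, difference 10 points).**

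| *c* | Observed before | Observed after | Risk ratio | Difference (points) |
|---|---|---|---|---|
| 10% | 18.4% | 9.1% | 0.495 | 9.3 |
| 25% | 15.8% | 7.7% | 0.487 | 8.1 |
| 30% | 14.9% | 7.2% | 0.485 | 7.7 |
| 50% | 11.1% | 5.3% | 0.474 | 5.8 |
| 60% | 9.1% | 4.3% | 0.468 | 4.8 |

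If training has no effect and *c* is constant, the two observed rates are equal and the risk ratio is exactly 1.

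**Case 2: *c* changes with training, true failure stays at 20%.**

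| *c* before → after | Observed before | Observed after | Spurious risk ratio |
|---|---|---|---|
| 25% → 50% | 15.8% | 11.1% | 0.70 |
| 30% → 50% | 14.9% | 11.1% | 0.75 |
| 50% → 30% | 11.1% | 14.9% | 1.34 |
| 50% → 25% | 11.1% | 15.8% | 1.42 |

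The true risk ratio is 1 in every row.

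**The plan's power figures.** The stated 76% and 89% do not enter this check. They were not reproduced: a Hussey-Hughes calculation on the layout of Table 2, with the implementation cells empty, gave about 97% and 99%. That is a separate matter, so no loss of power is claimed here against the stated figures.

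**The case against.** The strongest reply is that this is one loose phrase in a condensed article, set against several sections that plainly keep these births in. A secondary outcome that could never occur is itself evidence that the literal reading was not meant. The data collection section describes extraction from clinical notes and mentions no filter on mode of birth, so nothing shows that any birth was dropped. The large spurious risk ratios need the caesarean share to double or halve with training while total failure stays fixed, and nothing in the protocol supports a shift of that size. With a constant share the planned modified Poisson model gives 0.487 or 0.474 where the truth is 0.50, and 1.00 where there is no effect.

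Much of this stands. The intent was very probably to include these births; the document does not show that they were lost; and Case 2 is an illustration of what could happen, not an expected bias.

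It does not dispose of the point. The eligibility rule governs collection as well as analysis, and the study reviews notes retrospectively at four sites. A site that searched only vaginal births would be following the protocol, and sites could differ. Even with a constant share, absolute rates are understated and the caesarean outcome is empty.

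**Conclusion.** The concern holds. As written, the first inclusion criterion contradicts the population, the caesarean exclusion, the primary outcome and a secondary outcome, and nothing in the article overrides it. The contradiction is certain and rests on no assumption.

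The size of the effect is conditional on a site having applied the rule literally, and on a caesarean share that the protocol does not give. At an assumed share of 25% to 50%, a true 20% failure rate would be recorded as 15.8% to 11.1%. Relative effects are nearly unchanged if the share is constant. They can be wrong in either direction, 0.70 or 1.42 against a true 1.00, if the share moves between those values with training. Because the conflict reaches the primary outcome and its denominator, it must be corrected before results are interpreted.

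**What to change.** Reword the first criterion along these lines: *a birth, vaginal or by caesarean section, took place within a study site during the applicable study period.* Make the second explicit on timing: *an instrument was applied to the fetal head before birth or before the start of caesarean section.* The second change largely restates the existing exclusion, but it lets the inclusion list stand alone.

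Then confirm, for each of the four sites and for both the pre- and post-training periods, that caesarean records were searched for a prior instrument attempt, and report the answer with the results.

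The text change is one or two sentences. The Ethics and dissemination section has data collection still running in July 2018, with the study ending on 31 August 2018, so the rewording mainly corrects the record. The confirmation is what protects the data. If a site did filter on vaginal births, its caesarean records must be queried again for both periods; otherwise the cost is one enquiry per site.
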